### Adverse event monitoring

An adverse event (AE) is defined as any adverse medical occurrence that takes place during the trial period. All information pertaining to AEs will be documented on the adverse event page(s) of the case report form (CRF). Additionally, the principal investigator (PI) will make a further assessment to determine whether an unexpected AE is associated with TCD.

### Sample size calculation

Based on published data (3), the median number of new DWI lesions in the control group was 2.0 (range 1.0–5.5). Fitting a negative binomial distribution to these data yielded an estimated mean of 2.3 and dispersion parameter k = 2.78. Assuming a 50% reduction (mean = 1.15) in the TCD group, with 80% power and a two-sided significance level of 0.05, a sample size of 110 patients per group is required. Inflating for 5% dropout gives 116 per group (total *N* = 232).

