## Abstract

**Background:**

Carotid artery stenting (CAS) is an effective revascularization procedure for internal carotid artery stenosis, but it is associated with a high incidence of perioperative cerebral embolism, with asymptomatic and symptomatic embolic events occurring in up to 40% of patients. Transcranial Doppler (TCD) has been shown to enhance fibrinolysis through sonothrombolysis and may reduce embolic burden during carotid interventions.

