**Sample size estimates:**

A total of 232 patients are required to detect a 50% reduction in the median number of new DWI lesions (from 2.0 to 1.0) with 80% power and a two-sided *α* of 0.05, accounting for a 5% dropout rate.

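### The 80% power at 110 per group belongs to a halving of the mean lesion count with overdispersion 2.78, not to the stated halving of the median from 2.0 to 1.0

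*Protocol article*

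**What the plan says.** The protocol article states the design effect on two scales.

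- **Abstract, Sample size estimates:** 232 patients are needed for a "50% reduction in the median number of new DWI lesions (from 2.0 to 1.0) with 80% power", on the median scale.
- **Methods, Sample size calculation:** the starting point is published data in which "the median number of new DWI lesions in the control group was 2.0 (range 1.0–5.5". It continues: "Fitting a negative binomial distribution to these data yielded an estimated mean of 2.3 and dispersion parameter k = 2.78". The effect is then set on the mean scale, "Assuming a 50% reduction (mean = 1.15) in the TCD group", and "with 80% power and a two-sided significance level of 0.05" the text concludes that "a sample size of 110 patients per group is required". A 5% dropout allowance raises this to 116 per group, 232 in total.

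The section Statistical analysis names a negative binomial generalized linear model with a log link for the primary endpoint. The treatment effect in that model is a ratio of mean counts.

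**The concern.** A negative binomial is fixed by its mean and dispersion, so its median follows from them. The stated fit can therefore be checked against the stated medians. The label k is ambiguous: some software uses it for the coefficient of μ² in the variance, some for its reciprocal. The article does not say which is meant. If no reading yields both the stated medians and the stated sample size, the power claim is attached to the wrong effect.

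Two things depend on this. The calculation is the only justification given for N. In addition, the section Quality control and data management lets the data monitoring committee recommend a change in sample size after an interim analysis at 50% follow-up. A re-estimation that starts from k = 2.78 would take either 2.78 or 1/2.78 = 0.36 as its planning overdispersion, and the two differ more than threefold in required n.

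**Working it through.** **Inputs (Sample size calculation; Abstract).** Control mean 2.3, TCD mean 1.15, k = 2.78, 80% power, two-sided α = 0.05, 1:1 allocation, stated medians 2.0 and 1.0.

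**Formula.** Write Var = μ + aμ². For the log ratio of two negative binomial means, per group:

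n = [1.960·√V0 + 0.8416·√V1]² / (ln 0.5)²

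V1 = 1/2.3 + 1/1.15 + 2a = 1.304 + 2a. The null variance V0 is taken in three customary ways: equal to V1 (unpooled); 2/2.3 + 2a (control mean in both arms); or 2/1.725 + 2a (average mean in both arms). Here (ln 0.5)² = 0.4805.

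**Reproducing the plan's 110: k read as a = 2.78.**
- V1 = 1.304 + 5.56 = 6.864.
- Unpooled: 7.849 × 6.864 / 0.4805 = 112.1.
- Control-mean null: V0 = 6.430, n = 107.1 to 107.2.
- Average-mean null: V0 = 6.719, n = 110.5.
- Power at 110: SE = √(6.864/110) = 0.2498; 0.6931/0.2498 − 1.960 = 0.815; power 79.2%. A simulation of the negative binomial model (600 runs) gave 79.8%.
- Dropout: 110/0.95 = 115.8, so 116. This is correct.

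Medians under this reading:
- Control: P(0) = (1 + 2.78 × 2.3)^(−1/2.78) = 0.487 and P(≤1) = 0.638. The median is 1, with quartiles 0 and 3.
- TCD: P(0) = (1 + 2.78 × 1.15)^(−1/2.78) = 0.597. The median is 0.

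**The other reading: k as size parameter, a = 1/2.78 = 0.360.**
- V1 = 1.304 + 0.719 = 2.024.
- n = 33.1 (unpooled), 28.0 (control-mean null), 31.4 (average-mean null).
- Power at 110: SE = √(2.024/110) = 0.1356; 0.6931/0.1356 − 1.960 = 3.15; power 99.9%.
- Control: P(≤1) = 0.423, median 2. TCD: P(0) = 0.382 and P(≤1) = 0.693, median 1. These are the stated medians.

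**Anything in between.** At mean 2.3 the control median stays at 2 only while a is below about 0.87. At that limit V1 = 1.304 + 1.749 = 3.053 and n (unpooled) = 16.34 × 3.053 = 49.9.

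| Overdispersion a (means 2.3 and 1.15) | Medians | n per group (unpooled) | Power at 110 |
|---|---|---|---|
| 0.36 | 2 and 1 | 33 | 99.9% |
| 0.87 | 2 and 1 (limit) | 50 | 98.6% |
| 2.78 | 1 and 0 | 112 | 79.2% |

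The power at a = 0.87 follows from SE = √(3.053/110) = 0.1666 and 0.6931/0.1666 − 1.960 = 2.20.

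**Other routes to 110.** One-sided tests, 90% power, mean-difference formulas, quasi-Poisson and Wilcoxon formulas were also tried with the stated inputs. None gave 110.

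**The case against.** The best defence is that the calculation is sound on the scale that matters. The planned model compares means. For a mean ratio of 0.5 with overdispersion 2.78, 110 per group gives about 80% power, and 116 and 232 follow correctly. On that view the abstract is only loosely worded. This stands, and it limits the point to the mismatch between the stated effect and the powered one.

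Two reservations also stand. First, the incompatibility is shown at the stated mean of 2.3, not for every negative binomial: mean 6.2 with a = 3.15 has medians 2 and, after halving, 1, and needs about 111 per group. That is not the fit the article reports. Second, the reading a = 2.78 is inferred. It is the best match to 110, but the article does not confirm it.

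A reader might go further in three ways that the document does not support.

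- **That the fit contradicts its source data.** The figure 5.5 cannot be a patient's lesion count, which suggests an interquartile range. If it is one, and if it covers all patients, negative binomials with quartiles 1, 2 and 5 to 6 have means of about 3.2 to 4.6, not 2.3. Both conditions are assumptions. If the summary covers only patients with lesions, the picture changes: the distribution with mean 2.3 and a = 2.78, restricted to patients with at least one lesion, has quartiles 1, 3 and 6, not far from the published figures.
- **That a median of 2.0 conflicts with the abstract's background.** That text speaks of "asymptomatic and symptomatic embolic events occurring in up to 40% of patients". It does not define these events as new DWI lesions at 24 hours, and it gives an upper bound. It cannot be turned into a proportion with zero lesions.
- **That the trial is underpowered.** Nothing here shows it. If the stated medians hold at mean 2.3, 110 per group is more than is needed.

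**Conclusion.** The stated medians, the stated mean and 110 per group at 80% power cannot all hold. At mean 2.3, about 110 per group goes with medians 1 and 0; medians 2 and 1 go with at most about 50 per group, and about 28 to 33 if k is the size parameter. The 80% power belongs to a ratio of means of 0.5 with overdispersion 2.78, not to the median effect in the abstract.

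This rests on the negative binomial named in the plan, the stated means, and the Wald formula for the log ratio. Whether the mean and dispersion suit the source data cannot be settled from the article. The point should be corrected, preferably before the interim look, but it does not undermine the primary analysis.

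**What to change.** 1. State the variance function next to k: Var = μ + kμ² or Var = μ + μ²/k.
2. In the abstract, replace the reduction in the median by a ratio of mean lesion counts of 0.5 (2.3 to 1.15).
3. Check in the cited source whether the median of 2.0 and its limits cover all stented patients or only those with lesions, and whether the limits are an interquartile range. Label them accordingly.
4. Correct the mean and dispersion if that check requires it.
5. Restate the power that N = 232 delivers, with a short sensitivity table over the dispersion.

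The cost is one check of the source, one re-run calculation, and rewording of the abstract sentence and one paragraph. Restating the effect and the power adds no patients. If the mean or dispersion changes, the stated power may move in either direction and should be reported as it falls.

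### The negative binomial behind 110 per group does not fit the summary it is said to be fitted to, so the stated 80% power is unsupported and could be too low or too high

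*Protocol article*

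**What the plan says.** Protocol article, Methods, Sample size calculation: from a published source, "the median number of new DWI lesions in the control group was 2.0 (range 1.0–5.5"). Then: "Fitting a negative binomial distribution to these data yielded an estimated mean of 2.3 and dispersion parameter k = 2.78". The effect is a halving of the mean: "Assuming a 50% reduction (mean = 1.15) in the TCD group". The result: "with 80% power and a two-sided significance level of 0.05, a sample size of 110 patients per group is required". Allowing for 5% dropout, this becomes 116 per group and 232 in total.

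The abstract, under Sample size estimates, states the same target in terms of medians. The 232 patients are needed to "detect a 50% reduction in the median number of new DWI lesions (from 2.0 to 1.0").

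The convention for k is not given. The abstract's Background also says that asymptomatic and symptomatic embolic events together occur in at most about 40% of patients.

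**The concern.** Two opposite conventions for a negative binomial dispersion are in common use: variance = mean + k × mean², and variance = mean + mean²/k. With k = 2.78 they describe very different data. The paragraph claims a chain from published summary to fitted parameters to sample size. If the parameters that yield 110 do not return the published summary, the chain is broken, and the power, the required size and the detectable effect do not belong to the model the plan says it fitted.

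This paragraph is the only justification given for N. The section on quality control also lets the DSMC recommend a change in sample size or early termination once half the participants have completed follow-up. Its rules are not shown, but planning values that do not fit their source are a poor reference for such a decision.

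**Working it through.** **Inputs.** Two-sided α 0.05, power 80%, control mean 2.3, TCD mean 1.15 and k = 2.78, all from Sample size calculation. Allocation is 1:1 (Randomization and intervention). The analysis is a negative binomial model with log link (Statistical analysis). Write variance = mean + a × mean².

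**1. Reproducing 110.** n per group = (1.960 + 0.842)² × (1/2.3 + 1/1.15 + 2a) / (ln 0.5)².
- a = 2.78: 7.849 × (0.435 + 0.870 + 5.56) / 0.480 = 112.1. With the variance under the null it is 109.8, and with the mixed form 110.5. Power at 110 is 79.2% by formula and 79.9% by simulation of the negative binomial test. The stated 110 is reproduced.
- a = 1/2.78 = 0.36: 7.849 × (0.435 + 0.870 + 0.719) / 0.480 = 33.1, so 34. Power at 110 is 99.9%.
- Dropout: 110/0.95 = 115.8, so 116 per group and 232 in total. This is correct.

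So 110 requires k to multiply mean².

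**2. Does either reading return the cited summary?**

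| | variance = mean + 2.78 × mean² | variance = mean + mean²/2.78 |
|---|---|---|
| Control variance | 17.0 | 4.2 |
| Control zeros | 48.7% | 18.7% |
| Control quartiles | 0 / 1 / 3 | 1 / 2 / 3 |
| Median, control and TCD | 1 and 0 | 2 and 1 |
| n per group for 80% power | 110 to 112 | 34 |

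The left column misses the median of 2, the lower value of 1, the upper value of 5.5 and the abstract's fall from 2.0 to 1.0. The right column matches the medians and the lower value, but not 5.5 and not 110.

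**3. The mean of 2.3.** If 1.0–5.5 is an interquartile range, no dispersion from 0.01 to 10 at mean 2.3 gives an upper quartile above 3, so the mean does not fit either. If 1.0–5.5 is a true range, as labelled, the variance at mean 2.3 cannot exceed (5.5 − 2.3) × (2.3 − 1.0) = 4.16, against the 17.0 used, and there would be no zeros, against 49%.

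**4. What matching distributions imply for a halving.** Negative binomials with quartiles 1, 2 and 5 to 6 were searched under two assumptions about whom the summary covers.

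| Summary covers | n per group | Power at 110 |
|---|---|---|
| All control patients (mean about 3.1 to 4.7, a about 0.47 to 1.50) | about 31 to 60 | about 97% or more |
| Lesion-positive only, 45% to 55% positive | about 90 to 133 | about 72% to 87% |
| Lesion-positive only, about 40% positive | about 146 to 166 | about 63% to 68% |

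Under the lesion-positive reading, the plan's own parameters (mean 2.3, a = 2.78) give, among the 51% with at least one lesion, P(≤1) = 0.30, P(≤2) = 0.47 and P(≤5) = 0.74. The quartiles are 1/3/6, which is close to the cited summary but still not a median of 2.

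**The case against.** The strongest objection is that the summary may describe only patients with lesions. If at most about 40% of patients have an embolic event, as the abstract's Background says, a median of 2 over all patients is hard to understand. A summary of lesion-positive patients would remove that conflict and explain a lower value of 1.0. The plan's parameters then come near the cited figures (1/3/6 against 1.0/2.0/5.5). This stands as a serious possibility. It does not rescue the paragraph, which attributes the summary to the control group without restriction and whose parameters still miss the median.

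The objection does remove two stronger conclusions that a reader might draw:
- **That the trial is overpowered, with 97% power or more.** This holds only if the summary covers all control patients and 1.0–5.5 is an interquartile range with lower quartile 1. If only the median of 2 and an upper quartile of 5 to 6 are matched, with the lower quartile free, n can reach about 101. Under the lesion-positive reading power can fall below 80%.
- **That k was fitted under one convention and entered under the other.** The medians suggest it, but the inverse reading also misses 5.5, and the documents do not show how the fit was made.

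It is also fair to say that a half-integer upper value makes an interquartile range likelier than a true range. The source is not at hand, so this too is only likely.

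**Conclusion.** The point stands in this form: k is undefined, and under neither convention do the stated summary, the stated fit and the stated sample size agree with one another. That conclusion rests on the article's own figures and holds whether 1.0–5.5 is a range or an interquartile range, and whether or not lesion-free patients are included.

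The direction of the error is not established. Depending on the population summarised, matching fits need from about 31 to about 166 per group, and power at 110 for a halving runs from about 63% to more than 99%. The ranges assume a negative binomial with the same dispersion in both arms and, for the lower powers, that about 40% of patients have lesions. The documents do not justify cutting or raising N = 232. The sample size basis should be corrected, but the point does not by itself show that the trial is the wrong size.

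**What to change.** 1. Check in the cited source whether 1.0–5.5 is a range or an interquartile range, and whether lesion-free patients are included. State both.
2. Write the variance function beside k.
3. Refit the mean and dispersion to that summary, and report the quartiles that the fit returns.
4. In Sample size calculation, replace the claim that 110 per group is what 80% power requires with the power for a halving, and the detectable rate ratio, that 110 per group delivers on the refit. Change the matching statement in the abstract. Do not presume that power will be higher or lower than 80%.
5. If variance = mean + 2.78 × mean² is kept as a deliberate choice, say so. Withdraw the claim that it was fitted to 2.0 (1.0–5.5) and the wording about medians falling from 2.0 to 1.0.

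The cost is a look at the source, a short recalculation and a rewording in two places. Correcting the text adds no patients or procedures. The downside is a public correction and a stated power that may come out above or below 80%. If it comes out below, the sponsor would have to consider the sample size openly.

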### Statistical analysis

Intention-to-treat analysis will be used. The primary endpoint will be analyzed using a negative-binomial generalized linear model with a log-link function. For volume of new cerebral infarcts, analysis of covariance (ANCOVA) will be used if normally distributed; log-transformation followed by ANCOVA or a non-parametric test (e.g., Mann–Whitney U test) will be applied for between-group comparison if the distribution is skewed. Number of new DWI infarcts >0.5 mL will be compared between groups using negative-binomial generalized linear model with a log-link function. For composite incidence of ischemic stroke, TIA, and death within 30 days, Kaplan–Meier curves will be plotted, and between-group event rates will be compared with the log-rank test. A Cox proportional-hazards regression model will be fitted to calculate the hazard ratio (HR) with 95% confidence interval (CI) for the TCD group versus the Control group.

All safety endpoints will be analyzed in the safety analysis set. Categorical variables (e.g., incidence of intracranial hemorrhage, serious adverse events) will be summarized as frequencies and percentages, with between-group comparisons performed using Fisher’s exact test. Continuous variables will be described as mean ± standard deviation or median (interquartile range) according to their distribution, and compared using t-tests or non-parametric tests as appropriate.

Exploratory analyses of multiple secondary endpoints will be conducted without adjustment for multiple comparisons; results are considered hypothesis-generating and should be interpreted with caution.

All statistical tests will be two-sided, with a significance level of *α* = 0.05; a *p*-value <0.05 will be considered statistically significant.

The primary outcome will further be analyzed according to subgroups: age (<60 years vs. ≥ 60 years), sex (female vs. male), history of diabetes (yes vs. no), history of hypertension (yes vs. no), degree of index vessel stenosis (70–84% vs. 85–99%), collateral status (poor vs. good). Differences in the primary outcome across the aforementioned subgroups will be evaluated by assessing the interaction effect between the pre-specified baseline variables and the primary outcome.

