### Randomization and intervention

Eligible patients are randomized 1:1 into the TCD group or control group via a computer-generated sequence, stratified by collateral status (poor vs. good) and age (≤65 vs. >65 years). In TCD group, patients will receive continuous TCD monitoring using a 1.6 MHz transducer insonating the ipsilateral middle cerebral artery (M1 segment, 55 mm depth) at 100% power output (0.274 MPa). The monitoring begins at femoral artery puncture and continues until 30–60 min after CAS completion. In the Control group, patients will only receive standard perioperative care without TCD monitoring. Both groups will receive guideline-based medical management. To ensure patient safety during prolonged continuous TCD insonation, we will continuously monitor the real-time Thermal Index (TI) and Mechanical Index (MI) displayed on the ultrasound system. For the 1.6 MHz transducer used in this protocol, TI is consistently < 1.0 and MI < 1.9, both well within diagnostic safety limits. The operator will also regularly ask the patient about any local discomfort or warmth during the procedure. Any reported symptoms will be documented as adverse events and reviewed by the Data and Safety Monitoring Committee.

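### Randomization is stratified by collateral status and age, but the two negative-binomial lesion-count models are not stated to include either factor; adding them costs almost nothing and may gain power.

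*Protocol article*

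**What the plan says.** Under Randomization and intervention, allocation is 1:1 and "stratified by collateral status (poor vs. good) and age (≤65 vs. >65 years").

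Under Statistical analysis, "The primary endpoint will be analyzed using a negative-binomial generalized linear model with a log-link function". The count of lesions above 0.5 mL gets the same model family and link. No covariate is listed for either model. Collateral status appears in that section only as one of six subgroup variables. Age appears only as a subgroup variable, split at 60, so the age factor used for randomization is not mentioned in the analysis section.

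For the 30-day composite, the section says "between-group event rates will be compared with the log-rank test" and adds a Cox model, again without strata or covariates.

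The Sample size calculation section reports that fitting a negative binomial to published data "yielded an estimated mean of 2.3 and dispersion parameter k = 2.78". It targets a halving of the mean, to 1.15, at 80% power and a two-sided 5% level, and concludes that "a sample size of 110 patients per group is required". A 5% dropout allowance raises this to 116 per group, 232 in total.

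**The concern.** When randomization is stratified, the analysis normally carries the stratification factors. They are known at randomization. If they predict the outcome, leaving them out puts their effect into the dispersion term and widens the interval for the rate ratio.

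Dispersion dominates the variance here. On the article's own inputs the variance term is 1/2.3 + 1/1.15 + 2 × 2.78 = 6.86, of which 5.56 (81%) is dispersion. Any part of it that collateral status and age explain is precision gained without extra patients.

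There is also a pre-specification aspect. Unless the SAP settles the matter, both an adjusted and an unadjusted primary result could be presented later. The article reports that 12 patients are already enrolled and plans an interim analysis at 50% follow-up, so the model should be fixed before then.

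**Working it through.** **Inputs from the article:** control mean 2.3; TCD mean 1.15; k = 2.78; two-sided α 0.05; power 80%; 110 per group; 5% dropout.

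**Inputs assumed:** the rate ratio g for each factor (1.0 to 3.0), a 50% split on each factor, and independence of the two. The documents give none of these.

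**Step 1: reproduce the stated sample size.** With variance μ + kμ² and no covariates:

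- Unpooled: n = (1.960 + 0.842)² × 6.86 / (ln 0.5)² = 112.1
- Null variance at the pooled mean (1.725): 110.5
- Null variance at the control mean: 107.1

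Rounded up, these give 108 to 113, within 3% of 110. Reading k the other way (variance μ + μ²/k) gives only about 28 to 33, so k is a dispersion in the first sense. Dropout: 110/0.95 = 115.8, hence 116 per group and 232 in total. The size therefore follows from a two-group calculation and does not depend on adjustment.

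**Step 2: how much dispersion the factors could explain.** Hold marginal dispersion at 2.78. Two independent factors with ratio g and 50% prevalence give 1 + CV² = [1 + ((g − 1)/(g + 1))²]². The dispersion left after adjustment is k_c = 3.78/(1 + CV²) − 1.

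- g = 1.5: 3.78/1.0816 − 1 = 2.49
- g = 2.0: 3.78/1.2346 − 1 = 2.06
- g = 3.0: 3.78/1.5625 − 1 = 1.42

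From the Fisher information at 110 per group, the adjusted model then has power 79.2% (g = 1.0), 80.2% (1.25), 82.1% (1.5), 86.3% (2.0) and 91.9% (3.0). The distance from 79.2% is not the gain. When the strata differ, the unadjusted model also does better than that formula predicts, so the two analyses must be compared on the same simulated data.

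**Step 3: paired simulation.** 1,500 trials per row, 110 per group, arms balanced within strata, each trial fitted with and without the two factors.

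| g per factor | Power unadjusted | Power adjusted | Difference (points) | Mean SE unadjusted / adjusted |
|---|---|---|---|---|
| 1.0 | 76.6% | 77.6% | +1.0 | 0.249 / 0.248 |
| 1.5 | 81.5% | 82.3% | +0.8 | 0.243 / 0.239 |
| 2.0 | 84.5% | 87.8% | +3.3 | 0.236 / 0.225 |
| 3.0 | 86.2% | 92.4% | +6.2 | 0.229 / 0.205 |

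With no treatment effect, rejection was 5.4 to 6.7% unadjusted and 5.8 to 6.6% adjusted (Monte Carlo error about 0.6 points).

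**Step 4: second simulation with unequal factor strengths.** 108 per arm, 2,500 runs, four equal strata:

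- Collateral 2.0, age 1.5: 80.9% unadjusted, 83.0% adjusted (+2.1)
- Collateral 3.0, age 1.5: 82.9% and 86.6% (+3.7)
- Neither prognostic: 78.7% and 77.9% (−0.8)

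Null rejection was 5.1 to 6.2% across both analyses.

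**The case against.** The strongest reply is that the article is silent on covariates and does not exclude them. A generalized linear model can carry them. The same section names ANCOVA for lesion volume, a method that takes covariates, and lists none there either, so the article may simply omit covariate lists. Such lists are usually in the SAP, which is not shown. This stands in part: the text cannot be said to prescribe an unadjusted analysis, only not to state an adjusted one. It does not remove the point. The section is otherwise specific (link function, fallback tests, six subgroups with cut-points), the sample size is a two-group calculation, and naming the randomization factors is a nearly free improvement whatever the reason for their absence.

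A second reply is that the gain is small and rests on assumed inputs. This stands too, and it limits the size of the claim. At ratios up to 1.5 the change is about a point, and in every prognostic scenario simulated the unadjusted analysis already exceeds 80% power.

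Three stronger readings are tempting but unsupported:

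- **That the stratifiers were chosen because they predict lesion load.** The article gives no reason for the choice and no association with lesion count.
- **That the unadjusted standard error is invalid after stratified randomization.** In both simulations, null rejection is close between the two analyses.
- **That the log-rank and Cox analyses also lose precision.** No event rate or hazard ratio is given, so nothing can be computed. The composite is secondary, and adjusting a Cox model changes the hazard ratio being estimated; it does not simply shrink its standard error.

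**Conclusion.** The point holds as a matter of efficiency and of matching analysis to design, for the primary lesion-count model and the model for lesions above 0.5 mL. The power figures apply to the primary model only. Adjustment changes its power by between about −1 point (neither factor prognostic) and +6 points (each factor tripling the lesion count), with about +3 at a ratio of 2.0 each.

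These figures assume 50% prevalence, independent factors and a marginal dispersion of 2.78 as the article states it. The true prognostic strength is unknown, so no single figure should be quoted as the loss. Type I error is essentially unaffected, and the total of 232 stands. This is an improvement the trial should make, not an error that invalidates the plan.

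**What to change.** State the primary model in the analysis section as log(mean lesion count) = treatment + collateral status (poor/good) + age. Enter age at the randomization cut (≤65/>65) or as a continuous term; the subgroup split at 60 does not serve this purpose. Use the same terms for the count of lesions above 0.5 mL. Report the unadjusted model as a sensitivity analysis. If the SAP already specifies this, a cross-reference is enough.

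The cost is one sentence, fixed before the interim analysis. Both factors are recorded at randomization, so no new data are needed. If neither factor proves prognostic, the loss is within about one point of power. The sample size should stay as it is: because prognostic strength is unknown, any gain is a margin and not grounds for enrolling fewer patients.

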### Outcome measures

Primary efficacy endpoint is number of new DWI lesions at 24 (±8) hours post-randomization. Secondary efficacy endpoints include total volume of new DWI lesions; number of lesions >0.5 mL; composite of ischemic stroke, transient ischemic attack (TIA), or death within 30 (±3) days.

Safety endpoints include intracranial hemorrhage within 24 (±8) hours; serious adverse events within 24 h.

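### Lesion volume: the log-ANCOVA option is undefined for patients with no new lesion, and the choice between it and a rank test is left open

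*Protocol article*

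**What the plan says.** The protocol article, Outcome measures, places the endpoint in the secondary tier: "Secondary efficacy endpoints include total volume of new DWI lesions". Under Statistical analysis the general principle is "Intention-to-treat analysis will be used", and no sentence restricts the volume analysis to patients who have a lesion.

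The rule for volume has two steps. First: "For volume of new cerebral infarcts, analysis of covariance (ANCOVA) will be used if normally distributed". Then, for the other case: "log-transformation followed by ANCOVA or a non-parametric test (e.g., Mann–Whitney U test) will be applied for between-group comparison if the distribution is skewed". The article does not say how normality or skewness is judged, what decides between the two skewed-case options, or what is done with a volume of 0.

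The same section describes the status of secondary results: "Exploratory analyses of multiple secondary endpoints will be conducted without adjustment for multiple comparisons; results are considered hypothesis-generating".

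**The concern.** A patient with no new DWI lesion has a total new-lesion volume of exactly 0. Such patients are expected in large numbers, and they are the successes of a treatment meant to prevent emboli. The logarithm of 0 does not exist, so the log option needs a further decision: leave these patients out, or add a constant. The first conflicts with intention-to-treat and compares subsets formed after randomization. The second makes the size of the estimated effect depend on an arbitrary number.

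Separately, the test is chosen from the observed data. Log-ANCOVA and Mann–Whitney address different hypotheses, and nothing in the text prevents the choice from being made after both results are known. At stake is whether the volume result can be taken at face value, even as supporting evidence.

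**Working it through.** **Inputs** (Sample size calculation): "Fitting a negative binomial distribution to these data yielded an estimated mean of 2.3 and dispersion parameter k = 2.78". The treated mean is half the control value, 1.15. The remaining inputs are 80% power, two-sided 0.05, 110 per group, and 116 after 5% dropout.

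**Step 1. Which reading of k did the plan use?** Take variance = μ + kμ² and the Wald test on the log rate ratio:

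n = (1.960 + 0.842)² × (1/2.3 + 1/1.15 + 2 × 2.78) / (ln 0.5)² = 7.849 × 6.864 / 0.4805 = 112.1, so 113 per group.

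With the null variance at the average mean the result is 110.5 (111); with the null variance at the control mean it is 107.1 (108). All lie within 3% of the stated 110, and 110/0.95 = 115.8 gives 116. Reading k as the size parameter (variance = μ + μ²/2.78) gives 26 to 34 per group, which does not reproduce 110. The dispersion reading is therefore the main case. The other is kept as a range, partly because the dispersion reading implies a control median of 1 lesion, while the size reading gives the stated median of 2.

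**Step 2. Expected share with volume 0.**

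| Reading | Formula | Control (μ = 2.3) | TCD (μ = 1.15) |
|---|---|---|---|
| k as dispersion | (1 + kμ)^(−1/k) | 7.394^(−0.360) = 48.7% | 4.197^(−0.360) = 59.7% |
| k as size | (1 + μ/k)^(−k) | 1.827^(−2.78) = 18.7% | 1.414^(−2.78) = 38.2% |

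Of 110 analysed per arm that is about 54 and 66 (119 of 220, 54%), or about 21 and 42 (63 of 220, 28%). The abstract's background also points to many zeros: "with asymptomatic and symptomatic embolic events occurring in up to 40% of patients" leaves 60% or more without an event, although that figure is not defined as new DWI lesions.

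With such a mass at zero the volume cannot be normal. The first ANCOVA branch will not realistically apply, and the trial will face the unguided choice in the skewed branch.

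**Step 3. Does the choice matter?** The article gives no lesion volumes. As an assumption, take lognormal volumes per lesion (median 0.1 mL, log-SD 1), counts from the planning model with k as dispersion, 110 per arm, and a t-test on the log scale in place of ANCOVA. Simulated results:

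| Analysis | Power | Geometric mean ratio, TCD/control |
|---|---|---|
| Log of positive volumes only | 30–34% | about 0.67 |
| log(v + 0.001 mL) | 51% | 0.49 |
| log(v + 0.01 mL) | 57% | 0.60 |
| log(v + 0.1 mL) | 64% | 0.75 |
| log(v + 1 mL) | 67% | 0.90 |
| Mann–Whitney, all patients | 53–55% | not applicable |

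Ranges are across repeated simulations. With k as size, the ratio moves from 0.27 to 0.88 over the same constants.

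**Step 4. Other ways the treatment could act (zeros dropped).** If TCD prevented every lesion in half of patients and did nothing in the rest, the positive-only log analysis gives a ratio of 1.00 and rejects in 4.5% of trials, while Mann–Whitney on all patients has 97% power. If TCD cleared only lesions below 0.1 mL, the positive-only ratio is 1.36, significant against TCD in 24% of trials, although no patient was made worse.

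**Step 5. Type I error.** Each test alone holds about 5%. Taking the smaller p-value of log(v + 0.01) and Mann–Whitney gives 5.6–6.3%; taking the smaller of positive-only log and Mann–Whitney gives 8.5–9.5%.

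**The case against.** The strongest reply is that the sentence already contains a workable test. Mann–Whitney runs on untransformed volumes with zeros as ties. A reader might infer that the volume rule cannot be followed at all; the text does not support that. Only the log option has the gap.

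A reader might also infer that patients without lesions will be excluded. The article never says so and declares intention-to-treat. An offset could be set in the full protocol or analysis plan, which are not shown. The counts in the working are therefore patients for whom the log is undefined, not patients the plan discards. This stands. An unstated offset alone would not be a finding; the data-dependent choice between two analyses is, because the article itself states it.

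A third tempting inference is that a log analysis would miss or reverse a real benefit. Under the article's planning values it would not: with zeros dropped, the ratio still favours TCD (about 0.67), the sign reverses in 6% of simulated trials, and a significant reversal occurs in 0.03%. Blindness or reversal needs one of the mechanisms in step 4, which the planning model does not contain.

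Finally, it would go too far to call the p-value invalid. The article does not describe choosing by p-value, the inflation in step 5 is modest for the offset version, and the endpoint is labelled hypothesis-generating. That label, however, deals with multiplicity. It does not supply a definition for the log option or say which analysis will be reported.

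**Conclusion.** The point holds in limited form. The log-ANCOVA option cannot be carried out on all intention-to-treat patients as written, and the choice between it and a rank test is open and data-dependent. The log is undefined for about half of controls and three-fifths of the TCD arm on the reading of k that reproduces the sample size, and for roughly one-fifth and two-fifths on the other. These shares rest on the article's count model. The power figures and ratios rest in addition on assumed lesion volumes, and they show that the choice matters without predicting the trial's result.

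Severity is minor. The endpoint is secondary and exploratory, the negative-binomial primary analysis accommodates zeros, and the sample size does not depend on this rule.

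**What to change.** Delete the normality-dependent choice and the log-ANCOVA option. Name one rank-based test on total new-lesion volume in all randomized patients with a scan, keeping zeros as the lowest tied rank. The Mann–Whitney test already named is sufficient; its stratified form (van Elteren), using the two randomization factors (collateral status, and age split at 65), is preferable because it matches the design. Report the win probability (the Mann–Whitney estimate) with a 95% confidence interval. Show volume among lesion-positive patients as description only, without a test.

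A stated offset or a two-part model would also close the gap, but the rank test needs the least change and no arbitrary constant.

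The cost is a change of wording. The downside is that the effect is expressed as a rank-based probability and not as a difference in mL. The article reports 12 patients enrolled at its initial submission, so an early amendment could be made well before outcome data are compared.
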